**Methods:**

The SIM study is a single-center, randomized controlled trial with a 12-month follow-up period. The aim is to identify the most effective method of follow-up regarding patient compliance with treatment. The tests will be performed in a mobile unit in easily accessible locations. The goal is to perform 10,000 rapid tests for syphilis. Patients with a confirmed diagnosis according to VDRL tests will be randomized to one of three arms: telephone, smartphone game, or conventional in-person follow-up. All analyses will follow the intention-to-treat principle.

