### Participants and recruitment

All adults aged 18 years and older will be invited to answer a questionnaire to collect socioeconomic and sexual behavior data and undergo rapid tests for syphilis, HIV, and hepatitis B and C in a mobile unit located in an area accessible to a large population. The unit will have different attractive features, such as free internet, charging areas for smartphones, and shaded and rest areas with screens, to increase the participation rate. All participants will receive an ecobag plus preservatives and lubricants. Participants with a positive rapid test will be invited to undergo confirmatory testing. This protocol was written following the Standard Protocol Items: Recommendations for Interventional Trials (SPIRIT) statement to define the clinical trial protocol.

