### Eligibility criteria

The study will be carried out in Porto Alegre, Southern Brazil. Participants who do not return after three contact attempts will be excluded from the study, as will pregnant women, participants who are not able to provide contact information, participants who are illiterate and those who underwent syphilis treatment within the previous 3 months.

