### Sample size

Considering a confidence level of 95%, an incidence rate of 93.7 per 100,000 inhabitants in the municipality of Porto Alegre [9], and an acceptable difference of 60.0 per 100,000 inhabitants, it is estimated that testing 10,000 individuals will be necessary to obtain an accurate prevalence of syphilis in the municipality. This sample will serve as the basis for the inclusion of patients in the clinical trial.

For the randomized clinical trial, another sample size calculation will be considered. Using a previous article in which 16.5% of the participants who were diagnosed with syphilis received appropriate treatment and 55.9% received inappropriate treatment as a reference, it is expected that at least half of the latter group will eventually receive proper treatment, for a total of 44.45% receiving appropriate treatment [17]. Thus, considering a sample size calculation to detect differences in the proportions of adequate treatments between groups, using a 95% confidence level, 80% power, and a maximum loss rate of 20%, 51 participants in each study group will be needed.

The primary goal of the study is to compare treatment adherence and follow-up among the three parallel study arms. The groups will be compared as a whole, and if relevant, pairwise analysis will be conducted. Such comparisons will be performed using the chi-square test and adjusted residuals when necessary. We will investigate the association between treatment

adherence and sociodemographic, sexual health, and sexual behavior variables as secondary outcomes. The association will be estimated by calculating crude and adjusted odds ratios (ORs) using logistic regression, also addressing confounding variables. Intention-to-treat analysis will be used to assess the clinical effectiveness of the intervention.

We anticipate a minimal number of missing values given that the study variables will be collected by trained researchers. However, data quality analysis will be applied to identify inconsistencies and missing data, and meetings with the researchers will be conducted to discuss missing data and prevent further inconsistencies.

A statistical significance level of 0.05 will be adopted for all statistical analyses. R software, version 4.0.3, will be used for the analysis.

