#### Intervention

The intervention strategies aim to increase adherence to treatment and monitoring and promote communication with sexual partners (Fig. 1). All intervention and conventional strategies followed the guidelines of the Clinical Protocol and Therapeutic Guidelines for Comprehensive Attention to People with Sexually Transmitted Infections of the Ministry of Health of Brazil [4].

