#### Strategy 3: Conventional follow-up

The conventional strategy involves compulsory notification by a healthcare professional, and the patient is directed to seek treatment and follow-up at the primary health care unit closest to his or her home. The outcomes will be accessed by reviewing data from the public health records.

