### Outcome assessment

Compliance with treatment for those in the mobile app arm will be assessed according to the uploaded game data provided by the participant and use of the app during the study period. Adherence to treatment for those receiving telephone follow-up will be assessed through routine phone calls and questionnaire questions about the date of examination and treatment. Adherence in the usual care arm will be assessed by information collected from the participant's medical record at their referral health unit. The primary outcome will be the percentage of the participants who finish all three doses of penicillin in the 3 weeks. The secondary outcome will be the percentage of participants who completed VDRL tests at 3, 6, and 12 months. We also evaluated the number of sexual contacts informed by each participant. The outcomes will be evaluated by self-declaration and by contacting the healthcare unit where the participants made treatment and follow-up.

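### The primary outcome counts only a three-dose penicillin course, but the stated entry rules do not limit the trial to people for whom that course is indicated

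*Protocol article*

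**What the plan says.** All references are to the protocol article.

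- **Primary outcome** (Outcome assessment): "The primary outcome will be the percentage of the participants who finish all three doses of penicillin in the 3 weeks". No other rule is given for a participant on a different course.
- **Who is invited** (Participants and recruitment): "All adults aged 18 years and older will be invited to answer a questionnaire".
- **Who is randomised** (Abstract, Methods): "Patients with a confirmed diagnosis according to VDRL tests will be randomized to one of three arms".
- **Who is excluded** (Eligibility criteria): "Participants who do not return after three contact attempts will be excluded from the study, as will pregnant women". People without contact information are also excluded, and so are "participants who are illiterate and those who underwent syphilis treatment within the previous 3 months".
- **What sets the treatment** (Intervention): "All intervention and conventional strategies followed the guidelines of the Clinical Protocol and Therapeutic Guidelines". In usual care (Strategy 3), "the patient is directed to seek treatment and follow-up at the primary health care unit closest to his or her home".
- **What the trial is sized on** (Sample size): "considering a sample size calculation to detect differences in the proportions of adequate treatments between groups", with 16.5% against 44.45% receiving appropriate treatment, 80% power, 20% loss and 51 per group.
- **Analysis set** (Abstract, Methods; Statistical analyses): intention to treat.

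**The concern.** The outcome rule presupposes one particular course. The entry rules do not. None of the five exclusions refers to stage, prescribed course or tolerance of penicillin, and the article does not say that every randomised participant is expected to receive three doses.

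The trial asks whether a phone call or a game improves adherence. For a participant on another course, the three-dose rule cannot measure that: the result is a failure even if every dose was taken on time. Intention to treat keeps the participant in the denominator. Such participants add only failures to each arm, so they shrink the absolute difference and understate the adherence rate. The sample size is built for 80% power, so there is little room for dilution if 20% are indeed lost.

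**Working it through.** **1. Reproduce the planned sample size.** Inputs from the Sample size section: p1 = 0.165; p2 = 0.165 + 0.559/2 = 0.4445; significance level 0.05 (taken as two-sided, since the article does not say); power 0.80; loss 20%.

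Two proportions, pooled variance under the null, no continuity correction, with mean p = (0.165 + 0.4445)/2 = 0.30475:

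n = [1.960·√(2·0.30475·0.69525) + 0.842·√(0.165·0.835 + 0.4445·0.5555)]² / 0.2795² = 41.4, so 42 per arm.

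Allowing for loss, 42 × 1.2 = 50.4, or 51, which is the stated figure. Dividing instead gives 42/0.8 = 52.5, or 53. The plan's figure is therefore reproduced. The number evaluable after the full loss is 42 by the formula, or 51 × 0.8 = 40.8, about 41, from the stated size. Both are carried forward.

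**2. Add participants who cannot meet the rule.** Let f be the share of each arm on a course other than three penicillin doses. The article gives no value for f, so a range is shown. Assumptions: f is equal in the two arms compared; all of these participants score as failures; the planned rates apply to everyone else. Each rate is then multiplied by (1 − f), and the difference becomes 27.95 × (1 − f) points.

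**3. Power.** Exact enumeration of the two-sided 0.05 Pearson chi-square test for two arms of equal size:

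| f (assumed) | Rates | Difference (points) | Power, 41 per arm | Power, 42 per arm | Power, 51 per arm |
|---|---|---|---|---|---|
| 0 | 16.5% vs 44.5% | 28.0 | 80% | 81% | 88% |
| 10% | 14.9% vs 40.0% | 25.2 | 74% | 76% | 83% |
| 20% | 13.2% vs 35.6% | 22.4 | 68% | 69% | 77% |
| 30% | 11.6% vs 31.1% | 19.6 | 60% | 61% | 69% |

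The 51-per-arm column applies if every randomised participant is analysed, for example with non-attenders counted as not complete, and the planned rates hold in that full set.

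**The case against.** The strongest reply is that the affected group is never shown to exist. The article names no other drug or course. Its wording elsewhere fits a single multi-dose injectable course: the telephone strategy speaks of a next dose, the game strategy of an injection, and the Discussion of penicillin only. The national guideline is cited but not shown, so what it indicates for whom cannot be established here. This stands as a limit on size: f may be zero, and the numerical effect would then be nil. It does not remove the gap, because no sentence states that the three-dose course applies to all.

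It could also be said that an article may leave scoring details to the full protocol or analysis plan. But the primary outcome and the exclusions are both stated here, and the difficulty is that one does not fit the other.

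Three further objections are right, and bound the point:

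- A reader might infer that the sizing endpoint contradicts the primary endpoint. The article does not define appropriate or adequate treatment, and the source of the rates is not shown. It may itself be a dose count, so a mismatch is possible but not demonstrated. If those rates already come from a mixed population scored by a similar rule, multiplying by (1 − f) counts the dilution twice.
- A reader might infer that a chance difference in course mix between arms would bias the comparison. Under randomisation that is sampling error, already covered by the test's error rate.
- Scoring completion of whatever was prescribed would be a poor repair. It depends on prescribing after randomisation, and it would credit completion of an inappropriate course.

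**Conclusion.** The point holds as a mismatch between the stated outcome rule and the stated population. Any randomised participant on a course other than three penicillin doses is a primary failure in every arm, regardless of adherence, and this pulls the arms together. The loss is proportional: the planned 28.0-point difference becomes 28.0 × (1 − f). At f of 10, 20 or 30%, power is 74-76%, 68-69% or 60-61% with 41-42 evaluable per arm, against 80-81% with none affected. With all 51 analysed it is 83, 77 or 69%, against 88%, so at f = 10% it remains above the planned 80%.

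These figures rest on an assumed f that is equal across arms, and on the planned rates applying to everyone else. The article supports neither a particular value of f nor the claim that f exceeds zero. The need to reconcile the text is established; the amount of power lost is not.

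**What to change.** Reconcile Eligibility criteria, Sample size, Intervention and Outcome assessment in one of two ways:

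1. If a single course is intended, state that all randomised participants have the three-dose course as their indicated treatment. The present outcome can then stand.
2. Otherwise, define the primary outcome as the percentage of all randomised participants who complete the full course indicated for them under the guideline already cited in the Intervention section, within the time set for that course. Record the indicated course before randomisation, so that the target cannot depend on later prescribing. Count anyone never treated as not complete. Keep the three-dose count as a supportive analysis in those for whom that course is indicated.

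Either way, say in Sample size what adequate treatment means, so that the planned rates and the outcome can be seen to refer to the same thing.

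The first option costs a sentence. The second costs one extra baseline field and gives an endpoint defined relative to each participant's course instead of one common count. Neither changes any treatment rule, and no view is taken on which course is right.

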### Specimen processing

Samples will be treated as biohazardous material, and specimen handling will be carried out in a biosafety cabinet. Once arriving in the laboratory, serum samples will be immediately fractionated. Two aliquots will be frozen at − 80°C as backup samples. All samples with positivity on the treponemal test (rapid test) will be subjected to a confirmatory nontreponemal test. The aliquot will be directly used for the VDRL and rapid plasma regain (RPR) tests. If the VDRL test is negative, an additional treponemal test will be used to confirm (TPHA) syphilis positivity. An online platform for data entry will be used by the study team to add participant data, rapid test results, biological sample information, and exam reports. Data will be monitored daily by the project statistician.

### Statistical analyses

Descriptive analysis will be performed to characterize the study population. The categorical variables will be summarized by absolute frequencies and percentages, while continuous variables will be described as the means and standard deviations or medians and interquartile ranges.

To compare proportions, the chi-square test and Fisher's exact test will be used. Student’s *t* test or the nonparametric Mann–Whitney test will be used to compare continuous variables.

The primary goal of the study is to compare treatment adherence and follow-up among the three parallel study arms. We will investigate the association between treatment adherence and sociodemographic, sexual health, and sexual behavior variables as secondary outcomes. The association will be estimated by calculating crude and adjusted odds ratios (ORs) using logistic regression. Intention-to-treat analysis will be used to assess the clinical effectiveness of the intervention.

A statistical significance level of 0.05 will be adopted for all statistical analyses. R software, version 4.0.3, will be used for the analysis [18].

### Monitoring and quality control

During the project development stage, operational manuals were developed along with the questionnaires to serve as general guidelines for conducting interviews, standardizing information, and solving general doubts. All researchers involved in the data collection will be trained using simulated interviews and biological sample collections.

A pilot study will be performed for one month to identify and correct problems with the interview, logistical and study procedures.

The participants will be informed about the study results through reports that will be provided at the mobile unit of the study.

Quality control will be performed through system reports, data entry control, and data enrollment auditing. During the project development stage, we established written policies for sample management and quality control in the laboratory handbook. All laboratory professionals were trained and certified by the coordinator team according to the study protocol. Those performing the VDRL tests are certified by the National Program of Quality Control (PNCQ).

A web-based platform will be utilized for biological sample tracking and test result recording on a daily basis. Samples will be carefully transported to maintain the integrity of the sample, with attention to temperature, preservation methods, special transport containers, and time limitations. Once the samples arrive in the laboratory, their label information, quantity, and condition for the requested tests will be verified. Frozen specimen aliquots will be tracked using the Freezer Web system. Test results will be photo-documented, and the images will be uploaded to a digital repository.

We will perform an interim analysis only at 6 months after the start of the randomization to assess adaptations such as sample size recalculations and changes in eligibility criteria. Additional analyses for study interruption will not be necessary due to the low risk of the intervention being applied. Additionally, we expect no adverse effects of this intervention.

#### Ethics and dissemination

The study was approved by the Research Ethics Board (REB) of the Hospital Moinhos de Vento and Health Secretariat of the Municipality of Porto Alegre. Written consent will be obtained from all participants after they have been informed about the study procedures. All participants will provide informed consent addressing the questionnaire and the storage and use of biological samples. Data entry will be protected by personal logins and will be available to only the main statistician after the interview is finalized. Authorship eligibility followed the CRediT guidelines.

### Steering committee

The study will not have a monitoring committee due to the nature of the intervention, which is of minimal risk to participants.

### Dissemination

The results of the study will be disseminated to the different stakeholders by providing reports to the Ministry of Health and state and federal government agencies, publishing articles in scientific journals, and presenting the results at scientific conferences and to the Municipal Health Committee, of which users are part of the Single Health System.

## Discussion

Syphilis has been diagnosed in laboratories for over 100 years. Testing is becoming increasingly cheaper, faster, less invasive, and easier. Treatment for this disease has been known for over 60 years, and penicillin is a cheap drug with no major adverse events. However, syphilis has been re-emerging in Brazil and in many countries around the world. The World Health Organization (WHO) estimates that 11 million new cases of syphilis occur each year in Latin America, with 70% occurring in Brazil.

Open syphilis lesions facilitate HIV transmission. Thus, preventing and treating syphilis could also reduce HIV transmission. Furthermore, coinfection with HIV may change the natural course of syphilis.

The increase in the number of syphilis cases has resulted in new challenges for health management, and new data to guide effective interventions to control the disease are needed. Some questions need to be answered so that better prevention and control strategies can be developed and perhaps generate new health policies. Our study intends to answer the following questions: What is the better e-Health strategy for enhancing treatment and monitoring in patients with syphilis? Will any of the interventions increase the communication with and treatment of sexual partners?

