### Study procedures

A paper-based questionnaire to collect sociodemographic, behavioral, and health information will be administered to all participants to check eligibility, and a rapid test for syphilis will be performed. All participants with a positive test result will undergo confirmatory testing. Upon the receipt of confirmatory test results, the participants will be invited to take part in the clinical trial, and a web-based questionnaire will be used to collect information such as age, sex, social class, education level, alcohol consumption, tobacco and drug use, risk for syphilis, history of hepatitis and other sexually transmitted infections (STIs), number of sexual partners, type of sex and condom use. The main objective of the trial is to test strategies to improve adherence to follow-up. Overall, to increase awareness regarding syphilis, all participants will receive informative folders on syphilis, HIV, and hepatitis prior to randomization. Adherence will be monitored by the number of accesses to the application and by successful telephone calls.

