#### Strategy 2: Follow-up using a game in a smartphone app

A thematic game will be developed to encourage treatment and monitoring in patients with syphilis. The game will be easy, similar to other commercial games such as Candy Crush (King), Bubble Shoote (Sukavaty), Block Puzzle (Honkong Sanyou), and Block Puzzle Jewel-puzzle game (Elimination Master) and can be played by different ages and different education levels. The first phase of the game will be open to all study participants regardless of their rapid test results and will have information about prevention strategies and sexually transmitted infections. In the second phase, the participants will be prompted by notifications via smartphone 2 days before the day of treatment, on the day of treatment, and every day for 14 days after the date they should have received the injection. The participant is awarded coins to buy clothing and accessories for his or her avatar if he or she reads the information about STIs and provides information about his or her partners. The participant passes the phase of the game when he or she has taken the medication doses and completed the VDRL test. In different game phases, the avatar takes the bus and travels to different capitals of Brazil, where syphilis infection rates are also high.

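### Partner treatment is part of a stated study question but of no outcome, and the one partner count is ambiguous and open to the game arm's reward

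*Protocol article*

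**What the plan says.** The Discussion of the protocol article gives two questions that the study intends to answer. The second is: "Will any of the interventions increase the communication with and treatment of sexual partners". It therefore has two parts, communication with partners and treatment of partners.

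The Intervention section states a narrower aim: "The intervention strategies aim to increase adherence to treatment and monitoring and promote communication with sexual partners". Partner treatment is not named there.

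Outcome assessment lists three things:
- The first concerns the participant's own treatment: "The primary outcome will be the percentage of the participants who finish all three doses of penicillin in the 3 weeks".
- The next is the share of participants who had their own VDRL follow-up tests done, at three time points up to one year.
- The last is the only one that mentions partners: "We also evaluated the number of sexual contacts informed by each participant".

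The same section gives the sources as self-declaration and the health unit that treated and followed the participant.

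On the game, Strategy 2 says: "The participant is awarded coins to buy clothing and accessories for his or her avatar if he or she reads the information about STIs and". The sentence then adds the second condition for coins, which is supplying information about one's partners. No reward is described for the telephone or conventional arm. Under Study procedures, the questionnaire at trial entry already collects "number of sexual partners, type of sex and condom use".

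**The concern.** A study question should map to at least one outcome. Here one half, partner treatment, maps to none. It is not a side issue for this trial: the Introduction names untreated partners, and the reinfection that follows, among the possible causes of the rise in cases. The Discussion links its questions to prevention strategies and possible new health policies.

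The other half, communication, rests on a single count whose meaning is open. One arm has an incentive that touches partner information and the other two do not. The main hypothesis expects that same arm to do best. A higher count under the game could then be read as better partner notification when part or all of it is rewarded disclosure.

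**Working it through.** **Step 1: question against outcomes.**

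| Part of the question (Discussion) | Outcome (Outcome assessment) | Source named |
|---|---|---|
| Treatment of partners | None; doses and VDRL tests are the participant's own | None; the health unit is the participant's |
| Communication with partners | Number of contacts informed | Self-declaration, not tied to an arm or time point |

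The first row is empty. No analysis of the listed outcomes can fill it.

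**Step 2: the two readings of the count.**
- *Contacts reported to the study.* The count then measures disclosure to the study team, not talking to partners. It is the kind of act for which Strategy 2 gives coins, in the game arm only.
- *Partners notified by the participant.* The count then does address communication. The coins reward a related but different act. The answer is still self-reported, and only one arm has been rewarded for partner information.

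**Step 3: which comparisons are exposed.** Three pairwise comparisons are planned: game versus telephone, game versus conventional, and telephone versus conventional. The first two include the rewarded arm. The third does not.

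**Step 4: scale.** The protocol gives no size or power for a partner outcome, so there is no figure on this point to reproduce. Its 51 per arm concerns the participant's own treatment and serves here only to set the number analysed. It does reproduce. With 16.5% versus 44.45%, mean 30.475%, two-sided 0.05 (sidedness assumed) and 80% power:

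n = [1.96·√(2·0.30475·0.69525) + 0.8416·√(0.165·0.835 + 0.4445·0.5555)]² / 0.2795² ≈ 41.4, so 42.

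42 × 1.20 = 50.4, so 51. (42 / 0.80 = 52.5 would give 53.) After a 20% loss, 51 × 0.80 = 40.8, about 41 analysed.

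The following inputs are assumptions, not in the documents. Partner numbers are Poisson with the same mean (2 or 3) in both arms. Half of partners are reported without coins, and a larger share with coins. The test is Mann–Whitney at 0.05, which Statistical analyses names for continuous variables, with 2,000 simulated trials per setting. The reported counts then have mean (partner mean × share reported): for 2 partners, 1.0 against 1.2, 1.4 or 1.6; for 3 partners, 1.5 against 1.8, 2.1 or 2.4. Share of trials with a significant difference:

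| Partner mean, n per arm | 50% v 50% | 50% v 60% | 50% v 70% | 50% v 80% |
|---|---|---|---|---|
| 2, 41 | 0.046 | 0.126 | 0.345 | 0.625 |
| 2, 51 | 0.0455 | 0.1505 | 0.42 | 0.7455 |
| 3, 41 | 0.0495 | 0.1795 | 0.4925 | 0.793 |
| 3, 51 | 0.0505 | 0.196 | 0.576 | 0.87 |

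This shows what a reporting incentive could do if it acted on the count. It is not evidence that it does.

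**The case against.** The article condenses a fuller protocol, where the definition, wording and timing of the count may be set out. That stands for the count, and it is why the coin argument can only be conditional. It does not rescue partner treatment: the article states both the question and the outcomes, and they disagree.

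The partner count is neither the primary nor the secondary outcome, partner treatment appears as a study question in one sentence of the Discussion, and the Intervention section claims communication only. This limits the weight of the point and stands.

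If the count means reported contacts, the coins are part of the randomised intervention and more reporting is a genuine effect of the game. That is fair. What would be wrong is to call that effect communication with partners.

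Some stronger readings are tempting but not supported:
- *The count is the very act that earns coins.* This assumes the first reading in Step 2, and the text does not settle it.
- *Game entries feed the count, or coins are paid per partner.* Neither is stated. Uploaded game data are named only for treatment compliance in the app arm.
- *The whole partner question is unanswerable.* It asks about any of the interventions, and telephone versus conventional involves no coins.
- *A raw count is biased because people differ in partner numbers.* Among participants with a smartphone, who can be allocated to all three arms, randomisation balances partner number in expectation. A denominator mainly helps precision and interpretation.

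**Conclusion.** The point holds in two parts of different strength. Without any assumption: partner treatment is promised as an answer and no listed outcome or source records it, so no estimate is possible.

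Conditionally: the count of contacts informed is ambiguous. In comparisons involving the game arm it may reflect the coin incentive, directly if it counts reported contacts and through self-report if it counts notified partners. The documents do not fix the size. The simulated range of about 13% to 87% significant results, against about 5% with equal reporting, rests wholly on the assumed reporting shares and partner means.

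Telephone versus conventional is untouched by the coin argument. So are the primary outcome, the VDRL outcome and the sample size. The changes are worth making because they are cheap and a stated study question depends on them.

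**What to change.** 1. Define the partner outcome as the number of partners whom the participant told of the diagnosis.
2. Collect it with one identical, unrewarded question at the same time point in all three arms, and do not use entries made in the game for coins.
3. Add to that question how many of those partners were treated, by participant report. If this is not collected, remove partner treatment from the question in the Discussion and make no claim about it.
4. Optionally, use the baseline number of partners as denominator. This needs a recall period that matches the follow-up question; Study procedures gives none.

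Cost: one or two questionnaire items and a wording change. Partner treatment would be known only from the participant's account. The conventional arm may need one brief added contact, since Strategy 3 describes obtaining its outcomes from public health records.
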